### 5.3 DATA COLLECTION/ASSESSMENT

The schedule for timing, frequency and method of collection of all trial data is summarised in Table 1. Assessments will be performed as close as possible to the required time point. Ideally the commencement of self-help CBT will begin 3 weeks after randomisation. The duration of the intervention and contemporaneous TAU is 4-weeks. Post-intervention measures will be taken in both groups in parallel (i.e. 6 weeks and 6 months post-randomisation).

The Case Report Forms (CRF) should be completed in black ballpoint pen, with unique participant ID number and initials recorded on the header of each individual form. Information entered incorrectly should only be amended on the original CRF prior to photocopying. Corrections should be made by deleting with a single line through the entry and writing the correct value alongside the box; all amendments should be initialled and dated. Once complete, the CRFs will be photocopied and the copy should be sent to SCTU. The originals should be filed in the appropriate site file folder at the site.

#### 5.3.1 *Psychosocial assessment*

The following outcome measures will be assessed at baseline, week 6 (+/- 2 weeks) and month 6 (+/- 4 weeks). These will be completed by both the intervention and TAU participants.

##### 5.3.1.1 *Hot flushes and night sweats assessment*

The HFNS Rating Scale measures the extent to which HFNS are problematic, distressing and interfere with daily life.[30] Three items are rated on a 10-point Likert scale where higher scores indicate the patient views their HFNS as more bothersome and interfering with life. A change of  $\geq 1.5$  points on this scale is considered clinically relevant.[13, 14] The HFNS Rating Scale also includes a subscale measuring HFNS frequency that asks men to estimate how many flushes/sweats they have had in the past week.

The HFNS Belief and Behaviour scale is a 22-item scale measuring types of beliefs and behaviours of men with HFNS. Subscales include: (i) beliefs about HF in social context (e.g. everyone is looking at me), (ii) beliefs about coping/control of hot flushes (e.g. when I have a HF I think they will never end), and (iii) beliefs about night sweats and sleep (e.g. if I have NS I'll never get back to sleep). HFNS Behaviours include (i) positive coping behaviour, e.g. accepting HFNS, using breathing and calming responses; (ii) avoidance behaviour. Originally used for women with menopausal symptoms, it has been modified for men.[31]

##### 5.3.1.2 *Quality of life*

QoL will be assessed using the EORTC-QLQ-C30. EORTC-QLQ-C30 is a validated 30-item questionnaire for assessing QoL of patients with cancer. Anxiety and depression

The GAD7 is a self-administered 7 item patient questionnaire (e.g., feeling nervous, restlessness) as both screening tool and severity measure for generalised anxiety disorder.[33]

The PHQ9 is a self-administered measure of depression/mood severity and treatment response. Patients are asked how often they were bothered by nine problems (e.g., trouble concentrating, poor appetite) over the previous 2 weeks.[34]

The WSAS is a self-report scale of functional impairment attributable to an identified problem. It has been used to study depression and anxiety. The five-item scale includes ability to work, home management, social leisure activities, private leisure activities and ability to form and maintain close relationships.[36]

##### 5.3.1.3 *Sleep*

The PSQI is a 19 item self-rated questionnaire that assesses sleep quality, latency, duration, disturbance and medication use, and daytime dysfunction. These are analysed in seven components and summed to one total score.[35] For the purpose of this trial, only item 6 of the PSQI will be used.

#### **5.3.1.4 ADT Compliance Questionnaire**

The questionnaire will ask patients to report whether they have received their ADT as planned.

### **5.3.2 Process Evaluation**

#### **CNS team**

To ensure a high-quality delivery, 2 key CNS team members per site will be interviewed as individuals or as a group (interviewee preference) before trial training to discuss topics including pre-intervention practice and perception of the intervention. Where possible, post intervention interviews will take place up to 1 month after the post-intervention group workshops and will explore topics including experiences of setting up and delivering the intervention, any impact on day-to-day working and potential for running the intervention in routine practice.

Additionally, CNS team members will be asked to complete The Normalisation Measure Development questionnaire (NoMAD) to aid reflection on NPT constructs and to quantify the perspective of those directly involved in the delivery of the trial.

#### **Patients**

Participants will have the option to be contacted by the research team to take part in an interview when completing the informed consent form for the MANCAN2 trial.

Semi-structured interviews will be conducted within 1 month of patient intervention completion. The purpose of the interview is to gain an in-depth understanding of their experiences of participating in the self-help CBT intervention, with attention given to the virtual nature of the pre-and post-intervention workshops and motivation to sustain use of the intervention.

#### **Medical staff**

A member of the medical team responsible for prostate care services, who is likely to impact on the adoption of interventions for routine care services, will be identified by the CNS team.

The purpose of this interview is to understand a medic's perception of the intervention, the process involved in running the intervention, including engagement with staff and patients, post intervention identification and treatment of men with HFNS and the potential for running the intervention in routine practice.

#### **Manager**

A member of management who has influence on the implementation of a new service, will be identified by the CNS team delivering the intervention and invited for interview.

The interview will explore; the process of encouraging CBT take-up in patients, how patients access the intervention, the potential for running the intervention in routine practice and if the intervention fits with organisational priorities.

All interviews will take place via phone or video conference at the interviewee's preference and last approximately 45-60 minutes. Interviews will be recorded, transcribed and pseudonymised for data analysis purposes and managed in accordance with the University of Southampton Research Data Management Policy.

For further information please refer to the MANCAN2 Process evaluation Manual.

### **5.3.3 Health Economic Assessment**

The economic analysis will estimate the costs of providing the CBT intervention, and the cost consequences of the intervention for NHS services and for costs borne by patients. However, an economic evaluation will be conducted only if the intervention proves to be effective, as defined by a  $\geq 1.5$  point improvement in the HFNS. The cost of the intervention will be reported regardless of its effectiveness. If effective, cost effectiveness will be expressed in cost per unit change in HFNS and per QALY, based on the incremental differences between arms.

A health economic plan will be drawn up and incorporated into a combined Statistical and Health Economic Analysis Plan. The identification and collection of costs will be undertaken using the following methods:

#### **1) NHS**

Data on the use of medication, primary care visits, and out-patient visits will be collected using the Resource Use Questionnaire. In addition, we will estimate out-of-pocket spending such as herbal remedies, acupuncture or alternative therapies and time off work due to HFNS. The cost of the intervention will be based on nurse logs to record staff training cost, and time to deliver the intervention. This information will be used for sensitivity analysis from a societal perspective. We will use an adapted form of the Client Service Receipt Inventory.[38] Intervention-specific resource use will be collected through nurse logs to record staff training cost, and time to deliver the intervention.

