| Reflections and questions post CBT group workshops
Number of length of supervision sessions | Supervision notes                                    | CNS                                         |                    |                      | X                     | X | X | X |             |             |
| Fidelity: pre and post intervention workshop delivery                                          | Audio recordings of virtual pre/post group workshops | CNS to record all pre/ post group workshops |                    |                      | X                     |   |   | X |             |             |
| Adherence: Self-Guided CBT Booklet                                                             | Patient Evaluation Questionnaire                     | Participant (intervention arm only)         |                    |                      |                       |   |   | X |             |             |

| Domain / data type                                    | CRF/Assessment questionnaire           | Assessor/person completing form                          | 12-16 Participants |                      | Week                                     |   |   |   |             |             |
|-------------------------------------------------------|----------------------------------------|----------------------------------------------------------|--------------------|----------------------|------------------------------------------|---|---|---|-------------|-------------|
|                                                       |                                        |                                                          | Screening          | Baseline & Randomise | Intervention delivery                    |   |   |   | Follow up   |             |
|                                                       |                                        |                                                          |                    |                      | 1                                        | 2 | 3 | 4 | 6           | 26          |
| Window                                                |                                        |                                                          |                    |                      |                                          |   |   |   | +/- 2 weeks | +/- 4 weeks |

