|            | 7. The level fidelity of CBT when delivered by the prostate cancer CNS team                                                                                                                                                                                                                                                                                  | - Audio recordings of the virtual (pre- and post) intervention group workshops. An independent person will rate a random selection of these for adherence to the treatment manual.                                                                                                                                                                                                                                                        |

|  |                                                                                              |                                                                                                                                                                                                                                                                                                             |
|--|----------------------------------------------------------------------------------------------|-------------------------------------------------------------------------------------------------------------------------------------------------------------------------------------------------------------------------------------------------------------------------------------------------------------|
|  |                                                                                              | -Workshop Attendance logs (completed by CNS) will measure patient compliance to the virtual pre and post group intervention workshops .
- Post-intervention questionnaire completed by patients will measure how much of the booklet/CD patients engaged with and what lifestyle changes they have made. |
|  | 8. Resource usage analyses                                                                   | -CNS team logs to record staff training cost, time to deliver intervention in a virtual capacity.
-Participant resource use questionnaire                                                                                                                                                                |

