### **5.2.2 Supervision**

Prostate cancer CNS team members will receive ongoing supervision of their delivery of the virtual self-help CBT. Supervision will be on a CNS driven basis. CNSs will be instructed that they can contact the study clinical psychologist if they have any issues or concerns or need to ask general questions. They will record reflections and any questions or problems after the virtual pre- and post-programme workshops and will email these to the study clinical psychologist who facilitated their training. Feedback will be given by video conferencing software, telephone or email. Data will be collected on number, length and topics covered during supervisory sessions.

Study training completion will be documented on the training log, which will be sent to SCTU.

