### **7.4 HEALTH ECONOMIC ANALYSES**

The economic analysis will take an NHS perspective to estimate both cost effectiveness (£ per change in HFRS) and cost utility (Incremental £/QALY) as well as a budget impact. QALYs will be estimated from EORTC using the SCHARR algorithm (<https://www.sheffield.ac.uk/scharr/sections/heds/mvh/cancer>).

Costs will include that of the intervention and on any changes in use of NHS services. As the intervention cost might differ between that in the trial and in routine practice, we will take two approaches, one detailing changes in CNS team total time allocations in each arm during the trial, and another collecting data on views of both the CNS team and managers on the extent to which the intervention could be incorporated into standard practice (and under what circumstances such as being included in training and in guidelines). While both these costs will be reported, the latter would be more relevant in estimating budget impact if implemented in routine practice. The cost of changes in service use will be based on a customised resource use patient questionnaire at 6 weeks and 6 months.

Estimates of both cost and QALY increments will be estimated for each patient and incorporated into the planned statistical analyses described above. If a clinically relevant gain in the primary outcome is found to be statistically significant, more detailed economic modelling will be carried out, to explore uncertainty and to extend the time frame beyond that of the trial. This will build on the recent cost effectiveness modelling for similar interventions for hot flushes in breast cancer.[39]

All relevant resource items identified will be costed using published national cost data (British National Formulary and Personal Social Services Research Unit, and NHS reference cost). Accumulated costs and QALYs per patient will be estimated by means of area under the curve. Where appropriate we will estimate incremental cost-effectiveness ratios (ICERs). We will estimate mean values and 95% percentiles using non-parametric bootstrapping. We will produce cost-effectiveness acceptability curves (CEACs) to illustrate the uncertainty of such estimates. Major assumptions made in the costing and QALYs will be tested by means of sensitivity analyses.

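### No cost item covers the study psychologist's supervision and feedback time, so the costing as written slightly understates the intervention cost

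*Protocol*

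**What the plan says.** The costing source is fixed in several places, always in the same terms.

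- Section 5.3.3, under the NHS heading: "The cost of the intervention will be based on nurse logs to record staff training cost, and time to deliver the intervention". The same paragraph says again: "Intervention-specific resource use will be collected through nurse logs to record staff training cost, and time to deliver the intervention".
- Section 2, objective 8 (resource usage): "CNS team logs to record staff training cost, time to deliver intervention in a virtual capacity".
- Table 1 names nurse logs, completed by the CNS, as the source for clinic costs, nurse time and training costs.
- Sections 3.1.6 and 7.4 describe two costing approaches. The in-trial one is "one detailing changes in CNS team total time allocations in each arm during the trial". The other draws on the views of the CNS team and managers about routine practice.

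Delivery is described more widely. Section 5.2.2 states: "Prostate cancer CNS team members will receive ongoing supervision of their delivery of the virtual self-help CBT". After the pre- and post-programme workshops the nurses write down reflections and questions and "will email these to the study clinical psychologist who facilitated their training". The psychologist then answers by video, telephone or email. The same section says: "Data will be collected on number, length and topics covered during supervisory sessions". Table 1 has a row for this, "Number of length of supervision sessions", whose source is the supervision notes. It is separate from the nurse-log cost rows.

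**The concern.** The psychologist's supervision and feedback exist because the CBT workshops are being delivered. Nothing corresponds to them in the TAU-alone arm. A positive cost that falls on one arm only and is left out lowers that arm's cost and therefore the incremental cost.

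The trial's case is that an existing CNS team can deliver what a clinical psychologist delivered in MANCAN1. The psychologist input that remains is therefore something a service considering adoption would want to see costed. Section 5.3.3 commits to reporting the intervention cost whether or not the intervention works, so the gap would show in the published cost under either result.

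**Working it through.** **Text check.** The protocol states no intervention cost, unit cost or supervision time, so there is no figure to reproduce. Each component of delivery can be set against the cost items:

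- CNS training time: nurse logs (5.3.3, objective 8, Table 1). Covered.
- CNS workshop delivery time: nurse logs. Covered.
- CNS time spent in supervision: plausibly covered, by the nurse-time rows of Table 1 in weeks 1 to 4 or by total CNS time in 3.1.6 and 7.4.
- Psychologist time as trainer: may be covered by staff training cost; the protocol does not say.
- Psychologist time in supervision and feedback: number and length of sessions are in the supervision notes, which no costing passage uses. Not covered.

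**Direction.** Cost per QALY = (intervention cost + change in NHS cost) / QALY gain. Leaving out a positive CBT-only term lowers the numerator, and with a positive QALY gain it lowers the ratio. The same holds for cost per HFNS point.

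**Illustrative size.** Inputs from the protocol:

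- 6 to 8 men per group and two CBT groups per centre (4.5); 7 men is used as the midpoint, so 14 CBT men per centre
- training of 6 + 3 = 9 hours (5.2.1)
- at least two CNS members per centre (3.3)

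Assumptions, not in the protocol: 0.5 to 2 psychologist hours per CBT group, GBP 50 to 80 per hour, and 1.5-hour workshops run by two CNSs.

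Omitted cost per CBT participant = hours × rate / 7:

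- Low: 0.5 × 50 / 7 = GBP 3.6
- High: 2 × 80 / 7 = GBP 22.9

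Omitted psychologist time per man: 0.5 / 7 = 0.071 hours to 2 / 7 = 0.286 hours.

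Logged CNS time per man:

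- Delivery: 2 workshops × 1.5 h × 2 CNSs / 7 = 6 / 7 = 0.857 hours
- Training: 9 h × 2 CNSs / 14 = 18 / 14 = 1.286 hours
- Total: 2.143 hours

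Share omitted, at equal hourly rates:

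- Of training plus delivery: 0.071 / 2.143 = 3.3% to 0.286 / 2.143 = 13.3%
- Of workshop delivery alone: 0.071 / 0.857 = 8.3% to 0.286 / 0.857 = 33.3%

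**Sensitivity.** Take 12 CBT groups (six sites) of 6 to 8 men, so 72 to 96 CBT men. With 15 to 60 psychologist minutes for each of the 24 workshops and GBP 50 to 100 per hour, the total is 24 × 0.25 × 50 = GBP 300 to 24 × 1 × 100 = GBP 2,400. Per man that is 300 / 96 = GBP 3 to 2,400 / 72 = GBP 33. The hours per group are the same as above; the wider range comes from the rates and group sizes.

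**The case against.** The best defence is that item-level costing belongs to the health economic plan announced in section 5.3.3, which is not at hand. Section 7.4 also says that every relevant resource item identified will be costed and that major costing assumptions will be tested. Section 5.3.3 says the cost is based on nurse logs; it does not say supervision is excluded, and the session data are collected anyway. This lowers the weight of the point but does not remove it. Section 5.3.3 sets out the methods by which costs are identified and collected, then names the source twice, and objective 8 names it again. A later plan could add the item, but it would be departing from the stated source.

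It is also fair that supervision is CNS driven, so the amount could be close to nothing.

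Several stronger readings are tempting, and the protocol does not support them:

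- A reader might add the nurses' own supervision time and so double the figures. That time may already be in the nurse logs or in total CNS time.
- A reader might infer that the psychologist's training hours are missing. Staff training cost can include them; the text is only unclear.
- A reader might count feedback based on workshop recordings. Section 5.2.4 makes this optional and places it under fidelity, so it is partly a research activity.
- A reader might conclude that the budget impact is biased. Sections 3.1.6 and 7.4 regard the second approach, built on staff views of routine practice, as more relevant to budget impact. That approach does not mention supervision, but it does not rest on the trial logs alone.
- A reader might say that cost per QALY will be understated in any event. Under section 5.3.3 it is produced only if the intervention is judged effective.

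**Conclusion.** The point holds in a limited form. As the protocol is written, the study psychologist's supervision and feedback time is in no cost item, although it falls only on the CBT arm and session number and length are already recorded. The reported intervention cost is then too low by that amount. If the economic evaluation is run, the trial-based incremental cost and, with a positive QALY gain, the cost per QALY are too low as well. The direction is certain only if some supervision takes place.

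The size is not derivable from the protocol. Under the assumptions shown it is about GBP 4 to 23 per CBT participant, roughly 3 to 13% of logged training plus delivery time. The 8 to 33% relative to workshop delivery alone describes the recurring part of the cost and should not be read as the share of the whole intervention cost. The primary outcome is unaffected. This is a small, one-directional omission that is cheap to correct.

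**What to change.** In section 5.3.3, section 7.4, objective 8 and the cost rows of Table 1:

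- Add the study clinical psychologist's supervision and feedback time to the intervention cost, with the supervision notes as its source.
- Ask for time spent on email feedback to be entered in those notes. Recording the number and length of sessions does not clearly capture it, and Table 1 has the CNS, not the psychologist, completing the notes.
- Show supervision as its own cost line, so that the routine-practice scenario can vary it.
- State that staff training cost includes the psychologist trainer's time.

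The cost is mainly wording, because session number and length are already collected. The additions are a short entry for email time and slightly more costing work. The stated cost of CBT becomes slightly less favourable.
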